## Abstract

**Background:**

Despite a world-leading educational system, an achievement gap in educational outcomes exists between children of refugee background and native-born peers in Finland. To offer targeted support for children at schools, we need to be able to reliably assess and understand the interplay of the aspects of children’s cognitive, social, and mental health functions that may explain the underachievement of refugee children.

This study tests a novel research-based, universally applicable screening battery for evaluating cognitive, social, and mental health functioning of children at schools and planning supportive actions. It aims to answer research questions about a) the cognitive, social, and mental health functioning of refugee children compared with non-refugee immigrant and native-born children, b) the interplay of these different functions among refugee and other children, c) whether implementing a screening battery can inform schools in planning supportive actions for (refugee) children, and d) whether such supportive actions result in improvements in cognitive, social, and mental health functioning.

**Methods:**

Four hundred fifty children aged 10–12 will be recruited from primary schools, including 150 children of refugee background, 150 of non-refugee immigrant background, and 150 native-born Finnish children. A screening battery including tasks and questionnaires on different aspects of cognitive, social, and mental health functioning will be used to assess the children in their classrooms at the start and end of a school year. Supporting information will also be collected from parents and teachers. The information gathered will be collated into class-level feedback reports for teachers and, with parental permission, individualized reports for multiprofessional student welfare bodies, for informing supportive actions. Correlational and latent profile analyses, ANOVAs, and linear regression will be used to answer the research questions.

**Discussion:**

This study will help clarify how the interplay of cognitive, social, and mental health factors may explain underachievement at school among refugee children. It will provide evidence about the extent to which a standardized screening battery could be helpful in informing and planning supportive actions for children at schools, and whether such supportive actions can lead to positive cognitive, social, or mental health outcomes.

**Trial registration:**

The study will be preregistered on the Open Science Framework.

## Background

### Aims and objectives

As refugee children from all over the world enter European classrooms, policy makers, educators, and researchers need to rethink their education “at home” in order to ensure quality and equality. At the end of 2022, 108.4 million people were forced to flee their homes due to conflicts, violence, fear of persecution and human rights violations, with more than half of this population children and adolescents [1]. In Europe, the war in Ukraine alone has forced millions of people to leave their homes. Around 12 000 Ukrainian children had arrived in Finland by the fall of 2022 [2]. Learning opportunities are vital for immigrant children’s wellbeing and life satisfaction [3]. Unfortunately, both Finnish and international comparative studies show that migrant children commonly underachieve academically, meaning that their school performance does not correspond with their cognitive capacity [4–6]. Even if Finland has a world leading educational system [7], these challenges are pronounced among refugee students. A recent comparative analysis of educational outcomes among refugee children in the Nordic countries shows that refugee students have lower school results than their native-born peers in compulsory education [8]. In Finland, the achievement gap in mathematics has been found even greater than in other Nordic countries, corresponding to two years of studies [9].

During our previous work with Finnish schools [10], we learned that a major reason for poor school performance among refugee and non-refugee immigrant children lies in difficulties detecting the core reasons and mechanisms behind learning barriers. The reasons and mechanisms involve cognitive, social, and mental health issues that should be assessed early on and in combination with each other. Further, Nordic schools have varying, and often insufficient, knowledge and competence on how to relate appropriately to a diverse group of refugee students with multifaceted needs [8]. In Finland, adolescents with immigrant backgrounds are at greater risk of unmet needs for support and help at school than native-born Finnish adolescents [11] and teachers feel that immigrant students lack consistent support structures [12]. We need objective, universal, and user-friendly tools to assess different factors that explain children’s capacity to follow teaching or carry out their tasks at school, which are at the core of children’s integration into the education system. Profile-based scientific information about relative, age-specific differences across refugee, non-refugee immigrant, and native-born children regarding cognitive and social capacity and mental health is not available, and supportive actions are therefore often ineffective.

One reason for migrant children’s academic underachievement may be their stressful experiences. Coping with these experiences uses up resources that would otherwise be used for learning. Pre- and postmigration traumatic experiences have indeed been found to be major risk factors for learning problems [13]. Stressful events are associated with mental health symptoms in a dose-dependent manner [14, 15] and as many as 20–48% of refugee children suffer from of posttraumatic stress disorder (PTSD) and depression, although many also show resilience [16, 17]. A recent nationwide, population-based study (*n* = 73 690) showed that first generation immigrant adolescents in Finland had significantly more mental health symptoms than their second-generation immigrant peers [18]. Studies among adults have repeatedly shown that struggling with trauma symptoms such as re-experiencing and avoidance may impair cognitive functioning, including general intelligence, executive function, attention, verbal skills, memory, and visuospatial skills (e.g., [19, 20]). Some researchers have also detected effects of such experiences on children’s abstract reasoning, concentration, memory and attention [21–23]. Moreover, diminished ability to think, concentrate, and make decisions are core symptoms of depression [24].

All these functions form the basis for learning at school, but research is lacking among children and adolescents. The vicious circle of trauma exposure also presents itself in findings that more trauma exposure may jeopardize social competence [25] and that students who have poor social relations also have more problems in academic adjustment [26, 27]. In addition, trauma survivors who have problematic peer relations exhibit more mental health problems [28–30]. There is some evidence that level of social competence may be associated with aspects of cognitive functioning mentioned above, but the studies so far have been carried out among adults [31] and very young children [32]. Again, we need full elaboration and replication with school-aged children.

In sum, we need to understand the interplay of children’s cognitive, social, and mental health functions to offer targeted and tailored help for children at schools. This is important for all children, but would also benefit immigrant and especially refugee children, for whom uncovering the challenges underlying school performance has for a long time been seen as challenging. Our project develops a research based, validated and universal tool, the Screening Battery (SB), for evaluating and supporting further action toward better cognitive, social, and mental health functions. In this project, we develop, pilot and implement this tool in Finnish schools, and collect groundbreaking data on the interplay of cognitive, emotional, and social mechanisms that may underlie school problems among refugee children. We will compare profiles between refugee children and non-refugee immigrant children as well as their native peers in these dimensions. We will also study the effectiveness of supportive actions informed by the results of the screening battery, and planned by the school, while controlling for other significant life changes over the study year.

### Research question

First, we want to find out how the cognitive, social, and mental health functions of refugee children compare with (a) same aged immigrant children without refugee background and (b) native-born children in Finland. We will also examine whether worse mental health (trauma-related and depressive symptoms) is linked with poorer cognitive function and social competence across the sample. We hypothesize based on earlier (limited) literature in the field, 1) that refugee children, for whom exposure to trauma is likely more common, exhibit lower levels of cognitive functioning compared to immigrant children without refugee background and native Finnish children, and 2) that mental health problems and poorer social competence explain this link.

Second, we will examine whether reliable evaluation of cognitive, social, and mental health functions of students can inform schools about supportive actions for refugee children and whether this process is different compared with non-refugee immigrant children and/or native-born Finnish children. We will look at whether children who scored above/under critical thresholds on our Screening Battery (SB) report receive supportive actions during the school year. If they do, we look at what kinds of actions inside and outside the classroom schools conduct for refugee children, and whether the output of the SB was utilized to plan this support We will further look at whether the actions are different compared to actions with non-refugee immigrant children and/or native-born Finnish children and whether the actions are different compared to actions that do not use the information produced by the screening battery.

We will also examine whether the supportive actions are reflected in cognitive, social, and mental health functions of refugee children within their first year in Finnish schools (after controlling for other significant life changes during the study year). We will investigate whether this effect is different compared to non-refugee immigrant children and/or native-born Finnish children and if the effect is different compared to actions not using the information produced by the screening battery. We hypothesize 3) that supportive actions informed by the findings of the screening battery have a stronger positive effect than other actions. Finally, we will examine whether improvements in mental health (trauma, depression, resilience) and social functioning during the school year are associated with better performance in cognitive tests.

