### Screening battery

The screening battery (SB) gathers many kinds of data about the participants using demographic survey questions, tasks, and questionnaires. The children answer questions and complete tasks, and data is also collected from parents and teachers. The battery contains standardized and universally applicable assessments of a) cognitive functions (general intelligence, working memory, self-regulation, and self-efficacy and decision making), b) mental health (symptoms and well-being), and c) social competence. Prior to T_1_, the research group will offer a half-day training to teachers and school psychologists participating in the study on how to use the screening battery and specifically its feedback function. During the training, initial ideas and resources on how to transform the feedback into supportive actions at schools will be discussed among participating teachers and school psychologists.

The screening battery uses the Gorilla online platform to administer questionnaires and tasks (https://gorilla.sc/). Results are then transferred via an API to a Microsoft Power BI feedback tool which compiles both anonymous general (for teachers) and personalized (for multiprofessional student welfare bodies with consent from children’s parents) feedback with data visualizations and recommendations for supportive measures for students. At the end of the school year, the SB is administered again for the same classes (T_2_). The data about any supportive actions (either using the information produced by SB or not) that children may have received during the school year is also collected. The data is collected from parents, teachers, and multiprofessional student welfare bodies. The child’s own experiences of the support received are also collected during follow-up measurements. The researchers, who are all licensed psychologists and specialists in child cognitive and social skills as well as in child mental health, will be available for consultations with the schools throughout the study year, in case the school has further questions or concerns.

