#### Parental report

**Demographic variables.** At T_1_, we ask background information such as parents’ age, country of birth, education, marital status, and housing arrangements are collected. We also ask parents to report on the child’s country of birth, current legal status in host country, time in host country, and reason of migration. We request this information from both parents and children. Parents would be more reliable informants on these questions, but in the likely situation that we are unable to reach all parents, we will have the child’s report on the same topics. If there is discrepancy in child and parent reports, we rely on parents’ report. At T_2_, we ask about significant life changes after T_1_. The questionnaire includes changes in legal status in host country, family composition, significant losses, or other changes in close relations and other significant life changes. At T_2_, we collect information on whether or not the information provided by the SB has been used for the child, and a list of supportive actions the child or family has received.

**Family functioning** is measured by 12 items from the General Functioning subscale of the McMaster Family Assessment Device (FAD) [54, 55]. The parent assesses on a four-point scale how much they agree with the descriptions of family functioning (0 = s*trongly agree*, 1 = a*gree*, 2 = d*isagree*, 3 = s*trongly disagree*).

**Child language and development** is measured by 10 selected items from the Alberta Language and Development Questionnaire (ALDeQ) [56]. The selected items were chosen to reflect the parents’ view of the general development of the child and possible challenges in it, as well as parents’ own reading or learning difficulties. The parent evaluates each item on a four-point scale, but due to the varying form of the items, the answer categories vary between items (such as 0 = *never*, 1 = *rarely*, 2 = *sometimes*, 3 = *very much* or 3 = *very easy*, 2 = *easy enough*, 1 = *sometimes not easy*, 0 = *no, very hard*).

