To test Hypothesis 3, screening battery effects on cognitive, social, and mental health functioning will be evaluated using repeated measures ANOVAs with 2 × 3 for {T_1_, T_2_} and {children who received SB-based support, children who received non-SB-based support, children who did not receive SB-based support} among children who scored above/under critical thresholds, and following up with *t*-tests to compare means. Differences in SB-based actions will also be evaluated qualitatively. We will further use linear regression to test whether changes in mental health (trauma- and depressive symptoms) and social functioning associate with changes in cognitive functioning from T_1_ to T_2_. In addition to analyses in the whole sample, we will also do these analyses by subgroup, separately for our three groups. Classroom atmosphere, teacher self-efficacy and awareness of culturally responsive education, family functioning, child language and development as well as children’s cultural background will be used as covariates in the regression analyses and ANOVAs. Effect sizes and confidence intervals will be reported for main effects and p-value based inference will be de-emphasized based on guidelines for New Statistics [60].

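### The second research question follows only children past a threshold, with no comparison to the other children, so it cannot show that screening scores steer who is supported

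*Protocol article*

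**What the plan says.** The Research question section sets out the second question as a sequence. It starts with flagged children: "We will look at whether children who scored above/under critical thresholds on our Screening Battery (SB) report receive supportive actions during the school year". Where support was given, the study looks at the kinds of action and at "whether the output of the SB was utilized to plan this support". Two comparisons follow. One sets the actions for refugee children against those for the other two background groups. The other asks "whether the actions are different compared to actions that do not use the information produced by the screening battery". Children whose scores were not past a threshold are not named as a comparator.

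The Analysis plan gives no quantitative analysis of who receives support. The Hypothesis 3 analysis is confined to children past a threshold, and on the actions themselves the text says "Differences in SB-based actions will also be evaluated qualitatively".

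The data are wider than the analysis. The Screening battery section collects "The data about any supportive actions (either using the information produced by SB or not) that children may have received during the school year", without limiting this to flagged children. In the Parental report at T2, "we collect information on whether or not the information provided by the SB has been used for the child". The Teacher report records SB use and a list of actions at classroom level.

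Under Feedback tool, teachers receive anonymised class averages. Individual results go only to the student welfare body, on request and with parental permission.

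**The concern.** A rate of support among flagged children has no meaning for targeting until it is set against the rate among unflagged children in the same schools. If half of the flagged children are supported, the battery may have directed support to them, or half of all children may be supported whatever their score.

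The reported-use item helps, but in the second question it is put only to flagged children who were supported, so it too has no reference group. It says nothing about flagged children who received no support set against unflagged children who did. It also rests on reports by parents, who are not blinded, and by teachers whom the research group trained in the feedback function.

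At stake is how far the third aim in the abstract (whether the battery can inform schools in planning supportive actions) can be answered. The study could report that flagged children were supported and that the SB was used, and still not know whether any child's score affected who was supported.

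**Working it through.** **1. What each measure can separate.** Take four situations, all with 50% of flagged children supported. The rates are illustrative, and accurate reporting of SB use is assumed.

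| Situation | Flagged: supported | Supported flagged: SB used | Unflagged: supported | Difference, any support | Difference, SB-based support |
|---|---|---|---|---|---|
| A. SB ignored, support unrelated to score | 50% | none | 50% | 0 | 0 |
| B. SB ignored, support follows visible need | 50% | none | 30% | 20 points | 0 |
| C. SB used for class-wide actions | 50% | all | 50% | 0 | 0 |
| D. SB used, individual scores steer support | 50% | all | 30% | 20 points | 20 points |

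The plan's second question looks at the first two numeric columns.
- Receipt among flagged children is the same in all four rows.
- Reported use separates A and B from C and D. It does not separate C from D, that is, whether scores steered who was supported.
- The SB-based difference separates C from D.
- The any-support difference is positive in B although the SB was ignored, and zero in C although it was used. It cannot stand alone.

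Row C is realistic, since teachers see class averages and report classroom actions.

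**2. Background rate.** If support is independent of the score, P(supported | flagged) = P(supported). With 72 flagged children (16% of 450, assumed) and assumed background rates of 10%, 30% and 60%, the expected numbers supported are 72 × 0.10 = 7.2, 72 × 0.30 = 21.6 and 72 × 0.60 = 43.2. The flagged-minus-unflagged difference is 0 each time.

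**3. The plan's sample size and design effect.** Inputs from the Analysis plan are d = 0.5, alpha 0.05 (two-sided assumed), 80% power, mean cluster size 17 with variance 10, and ICC 0.07.
- Unclustered n = 63 per group.
- Design effect = 1 + [(1 + 10/17²) × 17 − 1] × 0.07 = 2.16.
- 63 × 2.161 = 136.2, or 8.01 clusters. Rounded up, 9 × 17 = 153, which agrees with the stated figure of about 150.

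**4. Precision of the added contrast.** The documents give neither the flagged share nor the support rates. Assume 50% v 30%, with 72 v 378 children.
- SE = √(0.5×0.5/72 + 0.3×0.7/378) = 0.0635.
- Pooled proportion = (36 + 113.4)/450 = 0.332. Null SE = √[0.332×0.668×(1/72 + 1/378)] = 0.0606.
- Power = Φ[(0.20 − 1.96×0.0606)/0.0635] = 90%, or 88% with the unpooled SE throughout.
- 95% CI half-width = 1.96 × 0.0635 = 12.4 points.
- Dividing both sample sizes by 2.16 gives SE 0.0933, power 61% (57% unpooled) and half-width 18.3 points.
- With 150 v 300, power is 98% without clustering and 80% with the full design effect.

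The full design effect is probably too harsh for a comparison within classes, which removes variation between classes. Splitting by whether the report was issued works the other way, because each part is smaller.

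**The case against.** The strongest reply is that the question does not stop at receipt. The next sentence asks about use of SB output, actions are compared with actions not using SB information, and parents and teachers report SB use. This stands. A reader might infer that the plan would answer yes whatever happened, or that an ignored battery and a used one would look alike. The documents do not support either inference: with accurate reporting, an ignored battery would show support without SB use (rows A and B).

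A second reply is that informing planning covers what is done as well as for whom, so a contrast in allocation answers only part of the aim. This is fair, and it is why the contrast belongs beside the reported-use item and should not replace it. Need-driven support and class-wide actions can each mislead the contrast, as rows B and C show.

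A third reply is that a condensed article may leave a descriptive comparison to the analysis plan, and nothing here rules it out. This limits the weight of the point but does not remove it. The Research question section itself names the measure and its comparators, and the one needed to interpret a receipt rate is not among them.

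**Conclusion.** The point holds in a limited form. As stated, the plan can describe support among flagged children and, through reported use, say something about whether the battery informed planning. It cannot show that scores steer which children are supported, because no comparison with unflagged children is stated. It should be corrected, but it does not invalidate the study.

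The conclusion about the missing comparison follows from the text and needs no assumed figure. The precision figures do rest on assumptions: 72 flagged children and 50% v 30% supported give about 90% power before clustering and about 57 to 61% with the full design effect of 2.16. Even with the contrast added, the study cannot isolate the effect of screening. Visible need confounds the any-support comparison, SB-based support depends on reported use, and there is no unscreened group.

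**What to change.** In the Research question and Analysis plan sections:
- Keep the reported SB-use item.
- Add the difference, with a 95% CI, in the proportion receiving SB-based support between children past and not past a threshold, comparing children within the same class. Give any support as a secondary contrast.
- Report the contrast separately by whether the individual report went to the student welfare body, since that is the main route by which one child's score can reach the school.
- Count class-wide actions separately from actions directed at an individual child.
- State that the any-support contrast is confounded by visible need, that there is no unscreened group, and that precision is limited.

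The cost is one added analysis on data that the Screening battery section already describes collecting, provided that support and SB use are recorded for unflagged children too. Intervals will be wide where few children fall on one side of a threshold or few individual reports are issued.
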